### Secondary outcome measures

#### Laboratory variables

In addition to Hb levels, haematocrit levels, ferritin levels, the TSI, the reticulocyte count and CRP levels are measured preoperatively, the day before surgery and at one, four and eight postoperative weeks. At the end of follow-up (8 weeks), the proportions of patients with anaemia (Hb below 12 g/dL) and without anaemia (Hb above 12 g/dL) and with iron deficiency (ferritin below 30 ng/mL) and without iron deficiency (ferritin above 30 ng/mL) are evaluated, together with the percentages of success in the full recovery of preoperative Hb levels among the patients in the study and control groups. Laboratory tests are conducted in the Hospital do Servidor Estadual and Hospital São Paulo laboratories, following the recommendations of the Brazilian Society of Clinical Pathology and Laboratory Medicine (Sociedade Brasileira de Patologia Clínica e Medicina Laboratorial – SBPC/ML). All instruments used in this study were subjected to internal (the manufacturer) and external controls through the Program of Excellence for Medical Laboratories (Programa de Excelência para Laboratórios Médicos) associated with SBPC/ML.

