## Abstract

**Background:**

Anaemia and iron deficiency are common complications following post-bariatric abdominoplasty. Given the low oral absorbability of iron resulting from bariatric surgery, it has been hypothesised that postoperative intravenously administered iron supplementation could be used to treat anaemia and to prevent the development of iron deficiency in these patients.

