## Methods/Design

### Trial design

This is a parallel, superiority, randomised controlled clinical trial with an allocation ratio of 1:1 (Table 1).

**Table 1 Tab1:** World Health Organisation (WHO) trial registration data set

Primary registry and trial identifying number	NCT01857011
Date of registration in primary registry	8 May 2013
Secondary identifying numbers	U1111-1169-6223, Brazilian Clinical Trials Registry (REBEC): RBR-2JGRKQ
Source of monetary or material support	São Paulo Research Foundation (Fundação de Amparo à Pesquisa do Estado de São Paulo – FAPESP), grant #2014/07710-6
Primary sponsor	Federal University of São Paulo
Secondary sponsor	Instituto de Assistência Médica ao Servidor Público Estadual (IAMSPE)
Contact for public queries	[name] ([contact])
Contact for scientific queries	[name] ([contact]
Public title	Iron Supplementation for the Treatment of Acute Anaemia After Postbariatric Tummy Tuck
Scientific title	Postoperative intravenously administered iron sucrose 200 mg administered twice or postoperative orally administered iron for the treatment of post-bariatric abdominoplasty anaemia (ISAPA): a randomised controlled trial
Countries of recruitment	Brazil
Health conditions or problems studied	Postoperative anaemia, iron deficiency
Interventions	Study group: administration of 200 mg of iron sulphate intravenously after post-bariatric abdominoplasty, immediately after the operation and on the first postoperative day
	Control group: ferrous sulphate supplementation orally administered postoperatively at a dose of 1 tablet of 100 mg 12/12 h for 8 weeks.
Key inclusion and exclusion criteria	Inclusion criteria: women; 18 to 55 years old; previous bariatric surgery; body mass index (BMI) less than 32 kg/m^2^; stability of weight loss for at least 6 months
	Exclusion criteria: smoking; cholelithiasis demonstrated by ultrasound; uncontrolled systemic diseases; bone marrow diseases; haematological disorders; presence of renal or hepatic insufficiency; acute infection; prior use of intravenously administered iron in the last 3 months; haemoglobin level less than 11.5 g/dL; ferritin level less than 11 ng/mL or greater than 100 ng/mL; transferrin saturation index below 20 % or exceeding 50 %; vitamin B_12_ level less than 210 pg/mL; folic acid level less than 3.3 ng/mL; albumin level less than 3 g/dL; C-reactive protein greater than 5 mg/L; mean corpuscular volume less than 80 fL
Study type	Interventional

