### Non-inclusion criteria

Illiteracy, tobacco use, cholelithiasis shown on ultrasound, uncontrolled systemic diseases, bone marrow diseases, haematological disorders, kidney or liver failure, acute infection, use of intravenously administered iron in the previous 3 months, prior anaphylactoid reaction with the use of intravenously administered iron, Hb levels less than 11.5 g/dL, ferritin levels less than 11 ng/mL or greater than 100 ng/mL, transferrin saturation index (TSI) greater than 50 % or less than 16 %, vitamin B_12_ levels less than 210 pg/mL, folic acid levels less than 3.3 ng/mL, albumin levels less than 3 g/dL, ultrasensitive C-reactive protein (CRP) levels greater than 5 mg/L, and mean corpuscular volume less than 80 fL.

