### Statistical methods: additional analyses

#### Adjusted analyses

The final mean Hb levels in the eighth postoperative week (primary outcome) will be adjusted for baseline Hb level, ferritin levels, and TSI via an analysis of covariance (ANCOVA). Both the adjusted and unadjusted analyses will be reported in the final publication.

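### Week-8 iron deficiency is a prevalence that includes women already below 30 ng/mL at entry, and the ferritin comparison makes less use of baseline ferritin than the planned ANCOVA of haemoglobin does

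*Protocol article*

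**What the plan says.** **Outcome definitions.** Under Laboratory variables, the week-8 outcomes include the share of patients "with iron deficiency (ferritin below 30 ng/mL") and "the proportions of patients with anaemia (Hb below 12 g/dL"). The text says these proportions are evaluated. It names no test or model for them and does not separate patients by their status before surgery. The registration table (Table 1) lists iron deficiency by serum ferritin first among the key secondary outcomes.

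**Entry limits.** Non-inclusion criteria bar "ferritin levels less than 11 ng/mL or greater than 100 ng/mL" and "Hb levels less than 11.5 g/dL". Table 1 repeats both limits.

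**Aim.** The abstract's Background gives, as a hypothesis, that intravenous iron could treat anaemia and serve "to prevent the development of iron deficiency in these patients".

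**Baseline data.** Hb, ferritin and the other laboratory variables "are measured preoperatively, the day before surgery and at one, four and eight postoperative weeks".

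**Analysis.** Under Statistical methods – outcomes, Hb and the iron profile are analysed by repeated-measures ANOVA, with t tests between groups at each time-point, or Mann-Whitney tests where normality fails. Under Adjusted analyses, week-8 mean Hb "will be adjusted for baseline Hb level, ferritin levels, and TSI via an analysis of covariance (ANCOVA"). No such adjustment is stated for ferritin. A full statistical analysis plan is promised before unmasking; it is not shown.

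**The concern.** The entry window and the outcome definition overlap. Ferritin from 11 to just under 30 ng/mL is eligible and already counts as iron deficiency. At week 8, a woman who was deficient throughout is counted together with one who became deficient after surgery. If the report then speaks of iron deficiency being prevented, this proportion alone cannot support that wording.

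The second part is efficiency. Baseline ferritin is collected the day before surgery, and the protocol already uses ANCOVA for Hb. For ferritin, the stated between-group test at week 8 ignores the baseline value, and repeated-measures ANOVA uses it less efficiently than ANCOVA. In a trial of 56 patients this loses power on the first-listed key secondary outcome.

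**Working it through.** **1. Number evaluable.** The protocol states a difference of 1.5 g/dL, SD 1.84, two-sided 5 %, power 80 % and 10 % loss. A t-based calculation gives 25 per arm (power 0.806). Then 25/0.9 = 27.8, rounded up to 28 per arm, or 56 in total. This reproduces the stated sample size, and 25 evaluable per arm is used below.

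**2. Overlap.** Eligible ferritin is 11 to 100 ng/mL and the outcome is below 30 ng/mL, so 11 to <30 ng/mL is both. For Hb, 11.5 to <12 g/dL is both, a band of 0.5 g/dL. The share of entrants with ferritin below 30 ng/mL is not given. Assumed lognormal ferritin truncated to 11–100 ng/mL (geometric mean 20 to 50, log-SD 0.5 to 0.9) puts it anywhere from 17 % to 76 %.

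**3. What the mixture does to a purely preventive effect.** All rates here are assumptions. New deficiency is 45 % (oral) against 15 % (intravenous) among those not deficient at entry. Persistence is 90 % in both arms among those deficient at entry. With a share q deficient at entry, the week-8 difference is

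[0.90q + 0.45(1−q)] − [0.90q + 0.15(1−q)] = 0.30(1−q).

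| q | Oral | Intravenous | Difference | Power, all patients (25 per arm) | Power, only those not deficient at entry (n per arm) |
|---|---|---|---|---|---|
| 0 | 45 % | 15 % | 30 points | 0.65 | 0.65 (25) |
| 0.2 | 54 % | 30 % | 24 points | 0.40 | 0.55 (20) |
| 0.4 | 63 % | 45 % | 18 points | 0.24 | 0.43 (15) |
| 0.6 | 72 % | 60 % | 12 points | 0.14 | 0.30 (10) |

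If treatment also corrects existing deficiency (persistence 90 % against 60 %), the difference stays at 30 points for every q. For q from 0.2 to 0.6 the all-patient comparison then has power 0.57 to 0.59, more than the restricted one.

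**4. Gain from baseline ferritin, like for like on the continuous scale.** Assumed: log-ferritin SD 0.6 and effect 0.4 log units, so the standardised effect is 0.4/0.6 = 0.67. The test is two-sided at 5 % with no multiplicity correction.

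- Unadjusted t test: noncentrality 0.667 × √(25/2) = 2.36 on 48 df, power 0.64.
- ANCOVA: noncentrality 2.36/√(1−r²) on 47 df, where r is the baseline to week-8 correlation.

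| r | √(1−r²) | Noncentrality | Power |
|---|---|---|---|
| 0.4 | 0.917 | 2.57 | 0.71 |
| 0.6 | 0.800 | 2.95 | 0.82 |
| 0.7 | 0.714 | 3.30 | 0.90 |

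The baseline-to-week-8 group-by-time contrast in a repeated-measures ANOVA compares changes. With equal SDs, its variance relative to the unadjusted test is 2(1−r), against 1−r² for ANCOVA: 1.20 against 0.84 at r = 0.4, 0.80 against 0.64 at r = 0.6, and 0.60 against 0.51 at r = 0.7. ANCOVA is smaller each time.

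**5. Gain for the proportion itself.** Simulation: 25 per arm, about 41 % below 30 ng/mL at entry, effect 0.45 log units, 1,500 runs per setting.

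| r | Unadjusted proportion | Baseline-adjusted logistic | t test, log ferritin | ANCOVA, log ferritin |
|---|---|---|---|---|
| 0.3 | 0.58 | 0.59 | 0.71 | 0.75 |
| 0.5 | 0.57 | 0.62 | 0.72 | 0.85 |
| 0.7 | 0.54 | 0.71 | 0.70 | 0.95 |

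With no true effect, the unadjusted proportion rejected in 6 to 7 % of runs. That reflects an uncorrected test in small samples and not the patients already deficient at entry.

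**The case against.** The strongest reply is that the week-8 proportion does what it is registered to do. Table 1 asks whether iron deficiency is present, which is a prevalence. Prevention appears as a hypothesis in the abstract's Background; the Objectives section speaks of beneficial effects on the iron profile. Randomisation makes the week-8 difference a fair estimate of the effect on prevalence. All of this stands, and it rules out several stronger readings:

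- *The outcome cannot show prevention.* A reader might infer this, but a preventive effect would still appear, diluted as in step 3. What is lost is the ability to tell prevention from persistence or correction.
- *The proportions will be compared unadjusted.* The article does not say so. It gives no method for them, and the announced analysis plan may. The definition of the outcome, however, is fixed in the article.
- *The baseline values are wasted.* They are not. Ferritin enters the repeated-measures analysis, and recovery of preoperative Hb uses baseline Hb. The loss is one of efficiency.
- *Chance imbalance in entry status invalidates the result.* The type I error of the test already allows for it.
- *The anaemia proportion has the same defect.* The overlap is only 0.5 g/dL, the stated hope is to treat anaemia, and week-8 Hb already has baseline-adjusted ANCOVA.

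It is also fair to say that setting an unadjusted proportion against ANCOVA overstates the value of adjustment, because part of that gap comes from dichotomising. Step 4 therefore compares the t test with ANCOVA on the same scale. For the proportion itself, adjustment gains little unless the correlation is high (step 5).

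**Conclusion.** The point holds as a limited one about ferritin. The overlap between entry and outcome is certain from the text. The week-8 proportion is a valid comparison of prevalence that does not distinguish new from persistent deficiency. The ferritin analysis stated in the article is less efficient than the ANCOVA already planned for Hb. At a standardised effect of 0.67 and 25 per arm, that ANCOVA would raise power from 0.64 to 0.71–0.90 for correlations of 0.4 to 0.7.

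The size of the gain rests on an assumed SD, effect and correlation, and the dilution in step 3 on an assumed entry share and event rates; the document gives none of these. The primary Hb analysis and the sample size are unaffected. It is an improvement worth making because it costs almost nothing.

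**What to change.** 1. Extend the ANCOVA under Adjusted analyses to week-8 log ferritin, adjusted for baseline log ferritin, and name it as the main iron-store comparison.
2. Keep the all-patient proportion below 30 ng/mL at week 8, compared by logistic regression adjusted for baseline ferritin (penalised if events are sparse). Describe it as prevalence.
3. Report descriptively, by arm, new deficiency among those with baseline ferritin of at least 30 ng/mL and resolution among those below 30 ng/mL. Use the words *development* and *prevention* only for the first group. Restricting the test to that group is not advised, since it discards patients and loses power if treatment also corrects existing deficiency.
4. The anaemia proportion needs no change; adjustment for baseline Hb is optional.

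The cost is a few sentences in the statistical analysis plan, which is still to be written before unmasking, and a few lines of analysis. Baseline ferritin is already collected, so no new data or visits are needed.

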#### Quality of life

Quality of life is assessed using a generic questionnaire (Short-Form 36 Health Survey (SF-36)) [52] and a specific questionnaire to assess fatigue and other anaemia-related symptoms (Functional Assessment of Chronic Illness Therapy – Fatigue (FACIT-F)) [53], both translated and validated for Portuguese, applied using an assisted self-administered questionnaire the day before surgery and then at one, four and eight postoperative weeks.

#### Adverse effects

Adverse effects will be estimated by measuring the differences between the two groups in regards to the proportions of mild (grades 1 and 2) and severe (grade 3, 4 and 5) adverse effects, which are possibly, probably, or definitely related to the use of iron supplementation during the follow-up period. Version 4 of Common Terminology Criteria for Adverse Events (CTAE v4.0) [54] will be used to grade adverse effects. The following adverse effects will be considered mild: transitory development of a skin rash, itching, tachycardia, tremor, dyspepsia, constipation, and nausea with improvement after discontinuation of medication or of symptomatic treatment. The following adverse effects will be considered severe: the maintenance of symptoms even after discontinuing the medication and treatment, need for hospitalisation, bronchospasm, anaphylactic shock and death. At each visit, patients will be asked about adverse events that have manifested since their previous visit. A standardised list containing the most common adverse effects of iron supplementation will be used. Cases where there is a need to definitively discontinue use of the medication will be considered treatment failures.

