### Interventions

Patients in the study and control groups undergo a mixed-type abdominoplasty, also known as anchor-line abdominoplasty, based on a previously published procedure [42], under general anaesthesia, coordinated by the same surgeon for all the operations.

Both the study group and the control group are instructed to maintain, postoperatively, routine vitamin and mineral supplementation for post-bariatric patients, ensuring that the supplement Materna® (Wyeth Laboratory, Markham, ON, Canada), which contains 60 mg of iron, 1 mg of folic acid and 12 μg of vitamin B_12_, among other elements, is taken daily after breakfast.

Patients in the study group receive intravenously, during the immediate postoperative period, 200 mg of ferric hydroxide saccharate (Takeda Pharma Ltd., Berlin, Germany) diluted in 200 mL of saline over 60 minutes. The same dose is administered on the first postoperative day post-bariatric abdominoplasty, totalling 400 mg of intravenously administered iron supplementation for each patient in the study group. The iron is administered by the nursing team as specifically recommended for the administration of intravenous iron, with monitoring of vital signs and possible adverse reactions [43].

Patients in the control group receive an additional postoperative orally administered supplementation of iron through the ingestion of one tablet of 330 mg of iron (III)-hydroxide polymaltose complex (equivalent to 100 mg of elemental iron) after lunch and another after dinner. Patients in the control group are instructed to maintain this additional orally administered iron supplementation during the 8-week follow-up period (Fig. 1).

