### Interventions – concomitant care

All patients are discharged on the second postoperative day and provided with prescriptions of antibiotics (cefadroxil, 500 mg orally 12/12 h), analgesics (dipyrone, 1000 mg orally 6/6 h) and anti-inflammatory drugs (celecoxib, 200 mg orally 12/12 h) for use during the first postoperative week. Suction drains are removed when drainage is less than 50 mL in 24 hours. A restrictive practice was adopted for blood transfusions, in which none of the patients receive blood transfusion while their Hb levels remain above 7 g/dL [51].

Patients receive a list with nutritional guidelines that advise them to eat six times per day, chew their food well, avoid fatty foods and sweets and include fruits and vegetables in their diet. The use of other food or vitamin supplements is not permitted other than those recommended by the study during follow-up.

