### Blinding

Due to the nature of the intervention (orally administered iron supplements result in blackening of the stool [62], facilitating the identification of the allocation group), we chose not to blind the patients or researchers to the allocation group. However, the surgeon who evaluates the incidence of local complications is blinded to the allocation group. In addition, the patients are not informed about the outcome of their laboratory tests to prevent the knowledge of their test results from influencing their responses on the quality of life questionnaires [63]. The use of an objective laboratory measurement as the primary endpoint (Hb level) also reduces detection bias.

Although unmasked clinical trials are subject to performance bias, the disclosure of allocation concealment at the end of the surgery reduces the possibility of surgical team performance bias during surgery. In addition, both the recommendation to use the same vitamin and mineral supplementation and the written supply of the same nutritional guidelines for all participants aim to reduce performance bias over the postoperative follow-up period.

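### The adverse-effect comparison counts only events judged related to iron, with no blinded assessor for that judgement, so attribution that differs by arm could bias it

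*Protocol article*

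**What the plan says.** All references are to the protocol article.

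- **Adverse effects.** The between-arm contrast is a difference in the proportions with mild and with severe effects, restricted to effects "which are possibly, probably, or definitely related to the use of iron supplementation during the follow-up period". The mild effects named are "transitory development of a skin rash, itching, tachycardia, tremor, dyspepsia, constipation, and nausea". Patients are asked at each visit about events since the last one, and "A standardised list containing the most common adverse effects of iron supplementation will be used". The section does not say who judges relatedness.
- **Blinding.** The authors write that "we chose not to blind the patients or researchers to the allocation group". The one exception is that "the surgeon who evaluates the incidence of local complications is blinded to the allocation group".
- **Interventions and concomitant care.** Every patient has general anaesthesia and abdominoplasty, and takes a daily supplement containing 60 mg of iron. Every patient is also prescribed an antibiotic, an analgesic and "anti-inflammatory drugs (celecoxib, 200 mg orally 12/12 h) for use during the first postoperative week". Study infusions are given immediately after surgery and on day 1. The control arm's tablets continue for 8 weeks.
- **Table 1.** The registered key secondary outcome is adverse events at 1, 4 and 8 weeks, with no restriction to related events.
- **Surgical complications.** Readmission, bleeding with an indication for transfusion, thromboembolism and death are compared between arms with no causality filter.

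**The concern.** A relatedness filter is a judgement made after the event. When the person making it may know the arm, and the symptom has several possible causes, the same symptom can be counted in one arm and dropped in the other. The comparison then mixes how often symptoms occur with how often they are blamed on iron.

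Three features of this trial make that possible. The listed mild symptoms are non-specific in patients recovering from surgery. The two arms have very different exposure windows, so timing alone can steer attribution. The Background also states an expectation by route: gastrointestinal effects with oral iron, and rare adverse effects with intravenous iron.

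At stake is the reading of one secondary outcome, the tolerability of the two routes. The broader set of events is registered and elicited at each visit, but the Adverse effects section compares only the judged subset.

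**Working it through.** **Plan's own figure.** The document gives no expected rate, difference or power for adverse effects, so there is nothing of that kind to reproduce. The only number used from it is 28 patients per arm. That figure does reproduce: a two-sample t-test with difference 1.5, SD 1.84, two-sided 5% and 80% power needs 24.6, so 25 per arm, and 25 / (1 − 0.10) = 27.8, so 28. It concerns haemoglobin only.

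**Does the text leave room for differential attribution?**

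| Question | What the text gives |
|---|---|
| Is the comparison filtered? | Yes, to effects at least possibly related to iron |
| Is a blinded assessor provided for the filter? | No; only the surgeon rating local complications is blinded |
| Are there other plausible causes in both arms? | Anaesthesia and surgery; week-1 drugs; 60 mg of iron daily |
| Is exposure to study iron alike in time? | No; to day 1 versus 8 weeks |
| Is the shared supplement inside or outside the term iron supplementation? | Not stated |

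That anaesthesia, surgery and the week-1 drugs can cause such symptoms is a general clinical premise; the document does not state it.

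**How a difference could arise.** Let p be the true proportion with a listed symptom, equal in both arms. Let a(oral) and a(IV) be the probabilities that it is judged related. The counted proportion in each arm is p × a, so

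spurious difference = p × (a(oral) − a(IV)).

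Every value of p and a below is an assumption.

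| a(oral) / a(IV) | p = 30% | p = 50% |
|---|---|---|
| 50% / 50% | 15% − 15% = 0 | 25% − 25% = 0 |
| 60% / 40% | 18% − 12% = 6 points | 30% − 20% = 10 points |
| 70% / 40% | 21% − 12% = 9 points | 35% − 20% = 15 points |
| 70% / 30% | 21% − 9% = 12 points | 35% − 15% = 20 points |
| 40% / 60% | 12% − 18% = −6 points | 20% − 30% = −10 points |

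In patients, 6 points is 28 × 0.06 = 1.7 and 20 points is 28 × 0.20 = 5.6 per arm.

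The chance that a two-sided Fisher exact test at 5% rejects, with 28 per arm and p from 30% to 60%, was obtained by enumeration. It is 1.5–2.7% with equal attribution (50% / 50%) and 7–22% with 70% / 40%. Moderate differential attribution would therefore more often distort the estimate than produce a significant result.

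**Same setting, all events counted.** The filter drops out and the expected difference is p − p = 0, provided that patients in both arms report alike.

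**Direction.** The last row of the table is not fanciful. Infusions are given with monitoring for reactions, so an early rash or tachycardia might be attributed more readily in the intravenous arm. The shared oral iron can also make a later gastrointestinal symptom in that arm possibly related.

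**The case against.** The strongest reply is that the filter is loose and its wording is neutral between arms. It asks about relation to iron supplementation, not to the allocated product, and both arms swallow 60 mg of iron a day. Constipation at week 4 in the intravenous arm can therefore qualify, and the threshold of possibly related is inclusive. This stands: it softens the bias and makes its direction uncertain. It does not remove the judgement, and the text does not say whether the supplement counts.

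A second reply is that parts of the safety assessment are already sound. There is a standardised list, which nothing in the text makes arm-specific, events are graded by published criteria, and serious outcomes such as readmission and death are compared unfiltered. This also stands, and it confines the point mainly to mild symptoms. It would be wrong to infer that safety as a whole is unprotected.

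Two further inferences are tempting and not supported. One is that tolerability is a main argument of the trial: the Objectives do not name it, the hypothesis rests on poor oral absorption, and the Background gives side effects of oral iron one sentence. The other is that the concomitant drugs explain symptoms throughout follow-up: they are prescribed for the first week only, so they do not account for a complaint that arises at week 4.

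Finally, an all-cause table could be left to the separate analysis plan that the article promises. That would answer a complaint about missing detail. Here the article itself fixes the comparison on the filtered subset, while Table 1 registers the unfiltered outcome.

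**Conclusion.** The point holds as a limited one. The stated counting rule leaves the adverse-effect comparison open to attribution that differs by arm, and no blinded assessor is provided for that judgement. The effect falls mainly on mild symptoms in one secondary outcome. The primary haemoglobin analysis is unaffected.

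A reader might infer that a false advantage for intravenous iron is bound to appear. The documents do not support that. Bias arises only if attribution differs between arms, and neither its size nor its sign can be derived from the text. That the assessor knows the arm is itself an inference from the Blinding section. The 6–20 points are illustrations that rest on an assumed equal symptom incidence of 30–50% and assumed attribution of 60% versus 40% or 70% versus 30%.

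**What to change.** In the Adverse effects section:

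1. Make the between-arm comparison on all adverse events reported at weeks 1, 4 and 8, whatever their judged cause. This matches the outcome registered in Table 1.
2. State that the planned standardised list is asked identically in both arms.
3. Report the related subset second, and state whether symptoms attributed to the shared 60 mg supplement count as related to iron supplementation.

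The events are already elicited at each visit, so the cost is a wording change and one extra table. No treatment or visit changes. By the Trial status section, 19 of the 56 patients had undergone surgery by August 2015 and recruitment was continuing, so at that date the rule could still be amended.

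There are two drawbacks. Background symptoms of surgery will add noise in both arms, which may dilute a real iron effect with 28 per arm. Counting all events also does not remove bias from patients who know their arm when they report symptoms; it removes only the added layer of attribution.

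### Adverse-effect severity is defined by two incompatible rules (CTCAE grade, and a list that uses persistence after stopping), and the protocol does not say which prevails

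*Protocol article*

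**What the plan says.** All of the severity wording is in one paragraph of the protocol article, under Secondary outcome measures, Adverse effects.

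- **Grade rule.** The arms are compared on "the proportions of mild (grades 1 and 2) and severe (grade 3, 4 and 5) adverse effects", limited to effects "which are possibly, probably, or definitely related to the use of iron supplementation during the follow-up period". The scale is fixed: "Version 4 of Common Terminology Criteria for Adverse Events (CTAE v4.0) [54] will be used to grade adverse effects".
- **List rule, mild.** A set of symptoms (rash, itching, tachycardia, tremor, dyspepsia, constipation, nausea) counts as mild. The set closes with "nausea with improvement after discontinuation of medication or of symptomatic treatment".
- **List rule, severe.** "The following adverse effects will be considered severe: the maintenance of symptoms even after discontinuing the medication and treatment", followed by hospitalisation, bronchospasm, anaphylactic shock and death.

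Neither list sets a grade, and no sentence ranks the two rules.

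The Interventions section gives the exposure times. In the intravenous arm the first infusion is given right after surgery, and "The same dose is administered on the first postoperative day". In the oral arm the tablets continue through the 8-week follow-up. Under Interventions – modifications, an oral-arm patient with gastrointestinal symptoms may cut the dose and carry on. On masking, the Blinding section states that "we chose not to blind the patients or researchers to the allocation group"; the one masked assessor it names judges local surgical complications.

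**The concern.** A CTCAE grade places an event on an ordered scale. Persistence after stopping describes its course relative to the drug. These are different attributes, so the two rules need not sort an event the same way. The mild and severe proportions are the trial's stated comparison of adverse effects of iron. With two rules in force, the reported proportions depend on which one the person classifying the event follows, and in an open-label trial that person can know the arm.

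The list rule also refers to the time at which the drug stops, and the two arms stop at very different times by design. It is therefore worth asking whether that rule could treat the arms unequally.

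**Working it through.** **1. The two rules applied to the same events.** The grades below are taken as already assigned.

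| Event | Grade rule | List rule |
|---|---|---|
| Constipation graded 1, persisting after the medication is stopped and treatment given | mild | severe |
| Nausea graded 3, improving after the medication is stopped | severe | mild |
| Nausea graded 1, persisting while tablets continue | mild | in neither list |

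The first two rows conflict in opposite directions. The third shows that the lists are also incomplete: the mild list asks for improvement, and the severe item asks that the medication has been stopped. If the improvement clause is attached to nausea only, constipation is also on the mild list by symptom type. The first row then shows the list rule contradicting itself as well as the grade rule.

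**2. What one reclassified patient is worth.** The only figure needed is the arm size. The Sample size section gives 28 per group. This reproduces: a difference of 1.5 g/dL, SD 1.84, two-sided 0.05 and 80 % power give 24.6, rounded up to 25 per arm by the t-test calculation, and 25 / (1 − 0.10) = 27.8, rounded up to 28. One patient is then 1/28 = 3.6 percentage points, or 1/25 = 4.0 points if 25 per arm are evaluable.

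**3. When the persistence item can apply.** Follow-up is 8 × 7 = 56 days.

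- *Intravenous arm:* the last planned dose is on postoperative day 1, leaving 56 − 1 = 55 of 56 days (98 %) after it. All three scheduled visits (weeks 1, 4 and 8) fall in that window.
- *Oral arm:* tablets are planned to week 8, so no day of follow-up lies after the last planned dose unless the patient stops early.

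The opportunity to meet the persistence item therefore differs between the arms if, and only if, completing the planned infusions counts as discontinuing the medication.

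**4. Size of any asymmetry.** This would need the rate of low-grade symptoms that persist despite treatment, and the share of oral-arm patients who stop early. The document gives neither, so no figure follows from it.

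**The case against.** The strongest defence is that CTCAE v4.0 is the only grading instruction and that the lists merely illustrate the two bands: passing or improving symptoms on one side, bronchospasm, anaphylactic shock and death on the other. Most listed items fit that reading. The persistence item does not, because it has no grade attached, and both lists are worded as rules for classification. The conflict stands.

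A reader might go further and infer that the list rule builds in a bias against intravenous iron, with the same lingering symptom counted severe there and mild in the oral arm. The documents do not support that as an established defect, for these reasons:

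- The severe item requires persistence after stopping the medication *and* after treatment. A symptom merely still present at the week-1 visit does not qualify.
- Elsewhere (the end of the Adverse effects paragraph, and the section on analysis population and missing data) the protocol uses discontinuation for a need to stop, which it counts as treatment failure. On that usage, completing two planned infusions is not discontinuation.
- An oral-arm nausea that persists on tablets falls in neither list. It becomes mild only through the grade rule, or later if it improves once the tablets are stopped.
- Both arms take a daily supplement containing 60 mg of iron. If that counts as the medication, the asymmetry shrinks.
- Significance figures can be produced, such as 6/28 versus 0/28 (Fisher p = 0.023), but they assume the counts and set the oral arm to zero. With an assumed true rate of 10 % in both arms, all intravenous cases and no oral cases counted severe, the chance of p ≤ 0.05 is only 5.5 %.

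Unmasked judgement of relatedness is a fair caution. However, the lack of masking is declared, events are elicited from a standardised list at each visit, and the systemic surgical complications are compared without a relatedness filter. Making all-cause events the main comparison would be a trade-off between approaches and would not correct an error.

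**Conclusion.** The point holds as a contradiction within one stated outcome definition. Two severity rules apply to the same proportions, they disagree in both directions, and neither is given precedence. This rests on the Adverse effects paragraph alone. It is not a detail left to the analysis plan, because the protocol fixes the definition and fixes it in two ways.

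Each affected patient shifts an arm's proportion by 3.6 points at 28 per arm; how many patients would be affected is unknown. Unequal treatment of the arms is a possibility that depends on reading completion of the infusions as discontinuation. The text does not settle that reading, and the size of any effect cannot be derived. The outcome is secondary and the primary haemoglobin comparison is untouched. The change should be made, but it does not threaten the trial's main result.

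**What to change.** - State that mild and severe, for the between-arm proportions, are defined by CTCAE v4.0 grade only (1–2 and 3–5), applied identically in both arms.
- Remove persistence after discontinuation as a severity criterion. Record persistence, discontinuation of study iron and the named events (such as hospitalisation, bronchospasm and anaphylactic shock) as separate descriptive variables, reported by type.
- Optionally, add a supporting table of all adverse events regardless of attribution, since relatedness is judged without masking. Its drawback is that it includes background postoperative symptoms.

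The cost is a wording change and at most one extra table. If the change falls under the Protocol amendments section, it also needs ethics committee approval. Trial status reports 19 patients operated on by August 2015, so events already recorded should be checked to confirm that each carries a grade.
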